### Treatment arms

The SARS-CoV-2 booster vaccination received while participating in the IMPROVE study will be delivered by the UK’s national vaccination programme.^30^ If another vaccine such as influenza is given at the same time, these data will be recorded.

#### Experimental arm

To suspend BTKi therapy for 1 week before and 2 weeks immediately after receiving the booster vaccination against COVID-19.

#### Control arm

To continue the same dose and regimen of BTKi therapy as usual in the week before and weeks after receiving the booster vaccination against COVID-19.

No concomitant care or interventions are prohibited in the study and the participants’ clinical care team will continue to manage their condition in the usual way after the end of their participation in the study.

Automatic reminders by Short Message Service (SMS) or email will be sent to participants to encourage adherence to their randomised intervention, where they consent to receive these. Participants may be telephoned by the study team if they decline the use of SMS or emails for reminders.

Participants and their usual care team will be able to manage any potential tumour flares including with steroids or any other drug as clinically appropriate. Should a clinical need arise, the participants’ usual care team will be able to advise them to continue or not with their allocation. It is known that tumour flare is fully reversible with the reintroduction of BTKi,^25^ and planned dose suspensions are common and do not appear to compromise long-term outcomes such as progression free or overall survival.^31^

### Outcomes

#### Primary outcome

SARS-CoV-2 spike RBD-specific antibody titre at 3 weeks postbooster vaccination (PBV).

#### Secondary outcomes

Levels of anti-spike RBD antibody at 12 weeks PBV.Participant assessments of disease activity: global assessment using a Numeric Rating Scale (NRS) with 1-week recall at baseline, 3 and 12 weeks PBV, current disease activity level and change since baseline, 3 and 12 weeks PBV.Disease flare-up (tumour flare) and actions taken to deal with them at 3 and 12 weeks PBV.Effect on QoL (assessed using European Organisation for Research and Treatment of Cancer -Quality of Life Questionnaire (EORTC-QLQ-CLL17)) at 3 and 12 weeks PBV.Adherence with advice to pause or continue BTKi: self-report at 3 weeks PBV.COVID-19 neutralising titre at baseline and 3 weeks PBV.T cell responses against ancestral Wuhan and the latest variant of concern (B1, B4, B5 and Sanofi) at baseline and 3 weeks PBV.

#### Exploratory outcomes

Effect on co-administration of influenza vaccination.

#### Safety outcomes

Serious adverse events (SAEs) that are related to study intervention (recorded from booster vaccination to 12 weeks PBV).

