### Objectives

Primary: Assess the effectiveness of a 3-week pause in BTKi, rather than continuing treatment as usual, on anti-spike-RBD antibody levels at 3 weeks post-SARS-CoV-2 booster vaccination.

Secondary and exploratory: Assess the effectiveness of a 3-week pause in BTKi treatment rather than continuing treatment as usual, on:

Anti-spike-RBD antibody levels at week 12 after booster vaccination.Neutralising antibody titres at baseline and week 3 after booster vaccination against Wuhan D614G and current variant of concern.Effect on T cell response to SARS-CoV-2 spike protein at 3 weeks postbooster vaccination.Responses to booster vaccination at 3 and 12 weeks after vaccination when influenza vaccination was given at the same time.Biochemical disease activity at weeks 3 and 12 postbooster vaccination.Disease activity changes and their tolerability as reported by participants during the 12 weeks postbooster vaccination.QoL at weeks 3 and 12 after booster vaccination.Self-reported adherence to the allocation.

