### Randomisation

This will be performed using a centralised validated computer randomisation programme through a secure (encrypted) web-based service, provided by the Oxford Clinical Trials Research Unit (OCTRU). Eligible participants will be randomised when they receive a date for their SARS-CoV-2 booster vaccination. The randomisation system will stratify on whether the participant is on their first line or subsequent line of therapy for CLL to ensure balanced allocation across treatment groups. It will use a 1:1 ratio to allocate to either continuing taking BTKi as usual or to have a 3-week pause (1 week before and 2 weeks after their booster vaccination against COVID-19).

Randomisation will be stratified on the line of CLL therapy being used as it has already been shown that the magnitude of immune response differs depending on the number of lines of therapy.^27^ We have chosen not to stratify on past COVID-19 infection even though it is a strong modifier of serological response to SARS-CoV-2 vaccines as it is difficult to ascertain this reliably from participant self-report. We are also not stratifying on the first vaccine platform received (eg, adenovirus vector or mRNA) as we have previously shown that there is no difference in the magnitude of antibody response by vaccine platform in patients with CLL,^27^ nor on which BTKi therapy the participant is currently taking. However, we will obtain past infection status using anti-nucleocapsid antibodies and use this in the statistical analysis. Due to the nature of the intervention, the participants and the clinical team will not be blind to the allocated arm of the study. However, those analysing the study samples will be blinded to the participants’ allocation. Trial statisticians will not be blinded.

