### Three weeks PBV (±4 days)

Information about any COVID-19 positive testing, a participant’s global assessment of disease activity will be collected, the latter using the same questions asked at the baseline visit asking for the last 7 days and also in the 3-week period since their booster. QoL will be assessed using EORTC-QLQ-CLL17. These data will be generally collected using a link to the study’s online REDCap database sent in a text message, or by email if participant prefers not to use a mobile phone for this purpose. If a participant prefers not to receive this survey link by email or text, this information will be collected by postal questionnaires or at the study visit.

The local research team will collect data at this visit about a participants COVID-19 vaccination history including the most recent COVID-19 vaccination received, details of any other vaccinations coadministered and adherence to the study intervention. In addition, details of any monoclonal antibody treatment will be collected and bloods taken and blood tests undertaken as at baseline. Details of any SAEs will also be recorded.

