The primary objective of the statistical analysis will be to identify if a temporary 3-week pausing of BTKi around the time of vaccination against SARS-CoV-2 increases the anti-spike-RBD antibody at 3 weeks postvaccine compared with continuing BTKi treatment without interruption. The anti-spike-RBD antibody levels will be summarised descriptively at baseline and 3 and 12 weeks post-COVID-19 booster vaccination follow-up. The differences between the study arms will be estimated using a mixed effects regression model, allowing for repeated measures clustered within participants. The model will be adjusted for a randomisation factor (first line or subsequent line of therapy), and prior infection status obtained from prevaccination antinucleocapsid antibodies, as fixed effects. A treatment by time interaction will be included. The model is anticipated to use an unstructured covariance matrix, and maximum likelihood estimation. Data will be log-transformed prior to analysis, as appropriate. The adjusted mean difference between the groups will be presented, together with 95% CI and p values. The regression model will be simplified (eg, linear regression) if the planned model does not converge.

Supplemental analyses will explore the time effect between the last COVID-19 vaccination dose and the dose given in IMPROVE. The effect of non-compliance to the randomised intervention will be explored using per-protocol analyses.

The same model as for the primary outcome will be used to analyse the 12-week PVB anti-spike-RBD antibody outcome. Similar supportive analyses as planned for the primary outcome will be performed for 12 weeks PVB data. Overall, 50% and 90% neutralisation by Wuhan and VOC along with, T cell spike response by subtype (spike for Wuhan and VOC, and nucleocapsid and membrane), will be analysed in a similar manner to anti-spike RBD antibody outcome. Other secondary outcomes will be analysed using generalised linear models for binary and continuous data, as appropriate, with model adjustment as described above.

The number of SAEs will be presented by treatment arm. The proportion of participants with at least one SAE will be compared. Details of the events will be presented, together with information on the timing of the events from randomisation.

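### SAE recording and the week-3 since-booster recall both open at the booster, a week after the BTKi pause begins, so the first 7 of 21 pause days lie outside them

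*Protocol article*

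**What the plan says.** Under Safety outcomes, the protocol article lists "Serious adverse events (SAEs) that are related to study intervention (recorded from booster vaccination to 12 weeks PBV"). This is the only place where it gives SAE recording a start and an end.

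The Experimental arm section defines the intervention: "To suspend BTKi therapy for 1 week before and 2 weeks immediately after receiving the booster vaccination against COVID-19". The Randomisation section agrees, describing a "3-week pause (1 week before and 2 weeks after their booster vaccination against COVID-19").

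At the week-3 visit, the participant's global assessment of disease activity is collected by "asking for the last 7 days and also in the 3-week period since their booster". The matching objective has the same anchor: "Disease activity changes and their tolerability as reported by participants during the 12 weeks postbooster vaccination".

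Two other statements do not fit a window that opens at the booster. The week-3 section says "Details of any SAEs will also be recorded", with no start date. The statistical analysis text (under Sample size and justification) will present SAE details "together with information on the timing of the events from randomisation". Randomisation comes before the booster: "Eligible participants will be randomised when they receive a date for their SARS-CoV-2 booster vaccination".

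**The concern.** The safety outcome concerns events related to the intervention, yet recording opens seven days after the intervention starts. The expected harm is known: the Introduction and Discussion name disease flare as the consequence of interrupting BTKi, and the Discussion says flare data will be gathered so that risk can be weighed against benefit. The trial also hypothesises that pausing will not significantly worsen control of the CLL.

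In the uncovered week, participants in the pause arm are off BTKi by allocation and control participants are not. If stopping causes any early excess of harm, that is the week in which a booster-anchored record would miss it. The omission therefore works in favour of pausing. Events that were never collected may not be recoverable at analysis.

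**Working it through.** **Inputs** (days counted from the booster, day 0)

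- Pause: day −7 to day +14 (Experimental arm; Randomisation).
- SAE window: day 0 to day +84, that is 12 × 7 (Safety outcomes).
- Week-3 visit: day 21 ± 4, so day 17 to day 25 (week-3 section heading).
- Week-3 recall: the last 7 days, and the period since the booster (week-3 section).
- Arm size: 120 randomised 1:1, so 60 per arm (Abstract).

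**The plan's own figure.** Pause length = 7 + 14 = 21 days, which matches the stated 3 weeks.

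**SAE window against pause.** Overlap = min(14, 84) − max(−7, 0) = 14 days. Uncovered = 21 − 14 = 7 days, and 7/21 = 33.3%. With all 60 pause-arm participants adhering fully, that is 60 × 1 = 60 of 60 × 3 = 180 on-pause participant-weeks.

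**Week-3 recall against pause.** The since-booster question reaches back to day 0, so it covers at most 14 of the 21 days. The 7-day question starts between day 17 − 7 = 10 and day 25 − 7 = 18. Neither reaches the week before the booster.

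**Other scheduled contacts.** Table 1 places Safety only at weeks 3 and 12, and disease activity at baseline, week 3 and week 12. The contact one week before vaccination is a reminder of allocation. The week-12 questions on NHS services and steroid courses look back only to the week-3 visit.

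**Missed booster.** The SAE window and both follow-up visits are dated from the booster. If it is not given, the window as written has no start. The article does not say how many such participants are expected.

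**Share of on-pause events lost.** The article gives no flare or SAE rate and no timing after stopping, so this needs an assumption. Let the daily hazard in the first pause week be r times that in the following two weeks. Share lost = 7r/(7r + 14) = r/(r + 2).

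| Assumed r | Share of on-pause events before the booster |
|---|---|
| 0 | 0% |
| 0.5 | 0.5/2.5 = 20% |
| 1 (constant hazard) | 1/3 = 33% |
| 2 | 2/4 = 50% |

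**Against the analysis text.** For any recorded SAE, time from randomisation is event date minus randomisation date, so it can be computed. But if recording opens at the booster, the interval from randomisation to booster contains no events by construction.

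**After the change.** Recording from randomisation, or from the start of the pause, covers 21 of 21 pause days (100%), against 14 of 21 (66.7%) now.

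**The case against.** Five counter-arguments deserve an answer.

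1. *The article is a condensation, and fuller SAE procedures may sit in the full protocol.* They may. But the point does not rest on missing detail: the article states a start, and that start is later than the exposure.

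2. *The undated SAE item at week 3, and timing from randomisation, suggest that earlier events are meant to be captured.* Perhaps so. Neither statement overrides the explicit window, and sites could read them differently. This is a reason to reconcile the text. A reader might go further and infer that timing from randomisation cannot be produced at all; that is wrong, since it can be computed for every recorded event.

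3. *Flare data are not wholly lost.* This stands. A reader might infer that all flare data exclude the first week, but the tumour-flare outcome under Secondary outcomes has no stated recall start. An early flare that persists could also show in the item on change from baseline, or in the week-3 blood count, film and LDH. What lacks a clear place is a pre-booster SAE, or an early flare that has resolved by week 3. The second is plausible, since the Control arm section describes flare as reversible once BTKi is resumed and lets the care team advise against continuing the allocation.

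4. *The window is identical in both arms.* Correct. It would be wrong to infer unequal follow-up, or that every lost event comes from the pause arm: background events in that week go unrecorded in both. The bias is limited to any excess caused by pausing.

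5. *The uncovered week is small relative to total follow-up.* From day −7 to day +84 is 91 days, and 7/91 = 7.7%. That is a fair measure of overall safety follow-up. For harm arising while off treatment, the 21-day pause is the relevant denominator.

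**Conclusion.** The point holds. The stated SAE window and the since-booster recall omit the first 7 of 21 pause days (33%), and the window sits badly with a randomisation time origin for reporting SAEs. The consequence is under-recording of any early harm attributable to the pause, in the direction that favours pausing.

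The day count is exact. The number of events affected is not known. The one-third figure for events holds only under a constant hazard over the pause, and the documents support neither that assumption nor another. The count of 60 participant-weeks assumes full adherence in a pause arm of 60. Participants who miss the booster are a further gap of unknown size, probably limited because randomisation waits for a booster date.

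This is a defect in safety ascertainment. It does not touch the primary endpoint, its model or the sample size.

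**What to change.** - Under Safety outcomes, record SAEs from randomisation in both arms until 12 weeks after the booster, or 12 weeks after the planned booster date if none is given.
- At week 3, extend the since-booster recall so that it also includes the week before the booster, worded identically in both arms.
- Reconcile the Safety outcomes entry, the undated SAE item in the week-3 section, and the SAE timing statement in the statistical analysis text, so that all three use the same start.

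The cost is a wording and CRF change and a few more SAE forms. The sample size and the primary analysis do not change.

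### The safety outcome is limited to intervention-related SAEs from vaccination onwards, while the collection and analysis text refers to SAEs without that limit; the arm comparison would be biased if the limited definition governed it

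*Protocol article*

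**What the plan says.** All references are to the protocol article.

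- **Safety outcomes** gives the only definition of the safety outcome: "Serious adverse events (SAEs) that are related to study intervention", with recording from the booster to 12 weeks after it.
- **Three weeks PBV** states "Details of any SAEs will also be recorded", and the Week 12 PBV section repeats this. Neither limits the record to related events.
- **Statistical analysis** (printed under Sample size and justification) says "The number of SAEs will be presented by treatment arm" and "The proportion of participants with at least one SAE will be compared". Neither sentence mentions relatedness. The text adds that the timing of events will be given from randomisation.
- **Randomisation** says "the participants and the clinical team will not be blind to the allocated arm of the study", and that "those analysing the study samples will be blinded to the participants’ allocation. Trial statisticians will not be blinded".
- **Control arm**: "To continue the same dose and regimen of BTKi therapy as usual in the week before and weeks after receiving the booster vaccination". The abstract labels the two arms intervention and usual care.
- **Experimental arm**: the pause begins one week before the booster and ends two weeks after it.

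**The concern.** A comparison between randomised arms is protected from bias when an event counts under the same rule in both arms. A rule that counts only events related to the study intervention can break this in three ways.

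1. The control arm simply carries on with usual treatment. On the plain reading, few of its SAEs could be called related to a study intervention, so whether an event counts depends on allocation.
2. Relatedness is a judgement, and the trial is open-label. Laboratory staff are the only people described as blinded.
3. The rule hides one side of the balance. The Introduction says that BTKi treatment raises bleeding risk. A serious bleed during continued treatment would not naturally be classed as related to the pause, so an event that pausing might avoid would go uncounted.

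The window adds a further problem. It opens at vaccination, after the pause has started.

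This matters because the article says that the trial will inform on both the benefits and the risks of pausing, and that the results will help to shape treatment guidance.

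**Working it through.** **Step 1: the statements side by side.**

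| Section | Which SAEs | From when |
|---|---|---|
| Safety outcomes | Related to study intervention | Booster vaccination |
| Week 3 and week 12 visits | Any | Start not stated |
| Statistical analysis | No relatedness limit; compared by arm | Timing given from randomisation |

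The first row differs from the other two in which events count, and from the third in time origin. The article does not say which rule defines an SAE in the comparison.

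**Step 2: the window.** The pause lasts 3 weeks and starts 1 week before the booster. A window opening at the booster omits 1 of 3 weeks, one third of the planned pause. Participants are randomised once their vaccination date is known, so any further time between randomisation and the pause is also outside it.

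**Step 3: size of the bias if the related-only rule governs.** The documents give no SAE rate or attribution rate, so there is no plan figure to reproduce, and the rates below are assumptions shown over a range.

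Inputs:
- n = 60 per arm (120 randomised 1:1, from the article).
- p = true risk of at least one SAE of any cause, equal in both arms: 5%, 10% or 15% (assumed).
- a = share of pause-arm cases called related: 20%, 30% or 50% (assumed).
- c = share of control-arm cases called related: 0% (assumed).

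Formulas: expected all-cause cases per arm = n × p; expected related cases = n × p × a against n × p × c; spurious difference = p × (a − c). The true difference is zero throughout.

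| p | All SAEs, pause v control | a = 20% | a = 30% | a = 50% |
|---|---|---|---|---|
| 5% | 3 v 3 | 0.6 v 0; 1.0 point | 0.9 v 0; 1.5 points | 1.5 v 0; 2.5 points |
| 10% | 6 v 6 | 1.2 v 0; 2.0 points | 1.8 v 0; 3.0 points | 3.0 v 0; 5.0 points |
| 15% | 9 v 9 | 1.8 v 0; 3.0 points | 2.7 v 0; 4.5 points | 4.5 v 0; 7.5 points |

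The extremes are 0.05 × 0.20 = 1.0 point and 0.15 × 0.50 = 7.5 points.

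If some control events are also called related, the bias shrinks but remains. With a = 30% and c = 10%, it is 1.0, 2.0 and 3.0 points for p = 5%, 10% and 15%.

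**Step 4: chance of a false-positive test.** Exact binomial enumeration with Fisher's test at two-sided 5% and 60 per arm gives:
- 50% v 0% attribution: 0.4%, 7.9% and 29% for p = 5%, 10% and 15%.
- 30% v 0% attribution: 0.03%, 0.9% and 5.3%.

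So in most scenarios the harm is a distorted estimate rather than a significant test.

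**The case against.** A reader might infer that the planned safety comparison counts only related SAEs, as judged by an unblinded team, and is therefore invalid. The documents do not support that, for these reasons.

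- **The comparison is not stated to be restricted.** The analysis sentences carry no relatedness limit, the visit sections record any SAE, and Table 1 schedules safety at weeks 3 and 12 without distinguishing the arms. Read alone, these describe an all-SAE comparison with the same capture in both arms. This stands: the defect is a conflict between statements, and the bias is conditional on how it is resolved.
- **No assessor is named.** The clinical team is unblinded, but the article does not say who judges relatedness or by what criteria. An article may leave this to the full protocol. This stands, so unblinded attribution is a risk and not a documented fact.
- **Continuing treatment could count as an intervention.** The article speaks of adherence to the randomised intervention for participants in general. On that reading control events could be attributed too. This stands in part: the usual-care label points the other way, and the bias disappears only if attribution is equal in both arms.
- **Harm is measured elsewhere.** Tumour flare, disease activity, quality of life and blood results are collected in both arms without attribution. This limits what is at stake, but none of them measures serious events of all causes.

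The numerical illustration rests wholly on assumed rates and on the related-only reading.

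**Conclusion.** The point holds as a contradiction with a conditional bias. The stated safety outcome, related SAEs from vaccination, does not match the collection and analysis text, which covers SAEs without that limit and times them from randomisation. Applied to the arm comparison, the stated definition would put attribution in place of randomisation and drop the first week of the pause. The resulting spurious excess in the pause arm would be about 1.0 to 7.5 percentage points, assuming equal all-cause risks of 5 to 15% and attribution of 20 to 50% against 0%. If the comparison counts all SAEs from randomisation in both arms, this bias does not arise, but that is not the outcome the article defines.

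The conflict should be settled before data lock, since the trial statisticians are unblinded and the choice between the two rules could otherwise be made with the arm-level data in view.

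**What to change.** Reconcile the sections as follows.

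- Define the safety outcome as all SAEs regardless of attribution, counted from randomisation to 12 weeks after vaccination in both arms.
- State that the week 3 record reaches back to randomisation and the week 12 record to the week 3 visit.
- Compare the proportion of participants with at least one SAE by a risk difference with 95% CI.
- List relatedness descriptively only, and say who assesses it.

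The sample size stays at 120. Any SAE is already recorded at both visits, so the cost is mainly wording, plus a little more SAE reporting for the period between randomisation and vaccination.

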#### Exclusion criteria

Insufficient time for applying the intervention prior to the planned COVID-19 booster vaccination.Diagnosed with alternative conditions requiring treatment with BTKi.Treated with anti-CD20 antibody therapy in the last 18 months or planning to start it.Concurrent immune suppressive treatments in the last 3 months specifically: methotrexate, ciclosporin, BCL-2 inhibitors, azathioprine, mycophenolate, prednisolone and biological agents.Any contraindications to COVID-19 vaccination.Richter’s transformation requiring active therapy.Radiotherapy or cancer chemotherapy in last 6 months.Active solid organ cancer (people with skin cancer or those cured of solid organ cancer are eligible).Receiving or has received in the past 6 months immunoglobulin replacement therapy.Receiving or has received in the past 6 months monoclonal antibody therapy against COVID-19 spike protein.

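### SAE recording opens at the booster, but the BTKi pause starts 7 days earlier, so the first 7 of 21 pause days (33%) fall outside the only defined SAE window

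*Protocol article*

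**What the plan says.** Under Safety outcomes, the protocol article gives one outcome and one window: "Serious adverse events (SAEs) that are related to study intervention (recorded from booster vaccination to 12 weeks PBV"). Under Experimental arm, the intervention is "To suspend BTKi therapy for 1 week before and 2 weeks immediately after receiving the booster vaccination against COVID-19".

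Randomisation comes before the pause. Under Randomisation: "Eligible participants will be randomised when they receive a date for their SARS-CoV-2 booster vaccination". The Exclusion criteria rule out patients with "Insufficient time for applying the intervention prior to the planned COVID-19 booster vaccination".

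The analysis text (under Sample size and justification) gives SAE numbers by arm and adds: "The proportion of participants with at least one SAE will be compared". It continues: "Details of the events will be presented, together with information on the timing of the events from randomisation".

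In Table 1, Safety is marked only at weeks 3 and 12 after vaccination. The week 3 visit section says "Details of any SAEs will also be recorded" and gives no start date for the look-back. The disease-activity questions at that visit are put "asking for the last 7 days and also in the 3-week period since their booster".

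**The concern.** The safety outcome is meant to catch harm from the intervention. The intervention is the pause, and the pause starts a week before recording does. An SAE in that week is outside the window as written, even if the investigator judges it related to stopping BTKi.

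That week is also the only part of the pause in which stopping BTKi acts without the vaccine, so an event then is easier to attribute. The Introduction and the Discussion both say that interrupting treatment can bring disease flare, and the strengths and limitations box says the trial will inform on the risks of pausing as well as the benefits. An incomplete SAE count for the pause arm weakens that side of the assessment.

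A second consequence follows from tying the window to the booster: a participant who is randomised but never boosted has no SAE window at all.

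**Working it through.** **Inputs, all from the protocol article**
- Pause: 1 week before to 2 weeks after the booster (Experimental arm). With the booster as day 0, this is day -7 to day +14.
- SAE window: booster to 12 weeks after it (Safety outcomes), which is day 0 to day 84.
- Week 3 visit: ±4 days, which is day 17 to day 25.
- Sample size: 120 randomised 1:1, so 60 per arm.

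**1. Reproduce the stated pause length.** 7 + 14 = 21 days = 3 weeks, as stated.

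**2. Pause days outside the window.** Days -7 to -1 are 7 days, and 7 / 21 = 33.3%. In planned exposure, 60 × 7 = 420 of 60 × 21 = 1,260 pause-days in the pause arm.

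**3. The same gap against total follow-up.** From pause start to week 12 is 84 + 7 = 91 days, and 7 / 91 = 7.7%. The gap is small against follow-up as a whole but large against the exposure of interest.

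**4. Does another stated element define SAE recording for days -7 to -1?**

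| Element | Reach | Defines SAE recording for that week? |
|---|---|---|
| Safety outcomes | Starts at booster | No, excludes it |
| Table 1, Safety row | Visits at weeks 3 and 12 | No look-back given |
| Week 3 visit, SAE details | No start date | No; may capture some events |
| Week 3 disease-activity questions | Last 7 days, and since booster | No |
| Secondary outcome: change in disease activity | Since baseline, so spans the week | No; a change rating, not an event record |
| Secondary outcome: tumour flare and actions taken | Reported at weeks 3 and 12, no start date | No; flare only |
| Full blood count, film, LDH | Baseline, week 3, week 12 | No; bracket the week, not events |
| SAE timing in the analysis | From randomisation | No; a time origin, not a collection rule |

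**5. After the fix.** Starting at day -7 covers 21 of 21 pause days. Starting at randomisation covers the same days plus the interval from randomisation to pause start, whose length the article does not give.

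**6. Look-back at the week 3 visit.** To day 0 it is 17 to 25 days. To day -7 it is 24 to 32 days.

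**The case against.** The strongest reply is that early harm is not invisible. Flare is the pausing harm the article names, and it has its own secondary outcome with no start at the booster. Participants also rate change since baseline, and bloods are taken before and after the pause. The week 3 section records any SAEs without a look-back limit, so sites may enter earlier events. This stands. A reader might infer that nothing in the plan touches the pre-booster week, and the documents do not support that. What may be lost is narrower: the formal SAE record for those days.

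Secondly, the article is condensed. It points to a full protocol and supplementary material that are not shown, and fuller SAE rules may sit there. That would excuse silence. Here, though, the article states a start point, and the stated point comes after the intervention begins.

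Thirdly, timing events from randomisation does not contradict a window that opens at the booster, because an event on day +5 can be timed from randomisation. This also stands. The mismatch shows only that the first stretch of the reporting timeline has no defined collection.

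Fourthly, a reader might infer that the loss can fall only on the pause arm. The documents do not establish this. The window applies to both arms, and the Introduction notes an increased bleeding risk from BTKi, so an SAE in a control participant who continued treatment that week would be excluded too. The SAE comparison in the analysis text is not restricted to related events, and how relatedness is judged is not shown.

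Finally, a reader might turn 33% of days into 33% of pause-period events. That needs constant risk over the pause, which is an assumption. If risk rises linearly from zero at stopping, the share is (7/21)² = 11%. If it falls linearly to zero at restart, it is 1 - (14/21)² = 56%. The article supports none of these shapes. It says most flares are mild, and eligibility requires that patients be considered able to pause without substantial risk of increased disease activity.

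**Conclusion.** The point holds as a defect in a stated rule. The only SAE window defined in the article misses the first 7 of 21 pause days (33%). A pause-related SAE in that week could be omitted from the by-arm counts and from the comparison of participants with at least one SAE. Each such omission lowers the pause-arm count, so it would tend to understate the risk of pausing. Neither the number of events nor the net effect on the between-arm comparison can be estimated from the document.

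The day counts rest only on the stated pause and window. The conclusion assumes that sites follow the Safety outcomes definition; if they read the week 3 instruction more broadly, the loss is smaller. The antibody outcomes and the sample size are not affected. The change should be made because the gap concerns the intervention's own risk and closing it costs little.

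**What to change.** Under Safety outcomes, record SAEs in both arms from randomisation, or at the latest from 7 days before the planned booster, to 12 weeks after the booster. If no booster is given, use the planned booster date to set the window. Have sites ask about this whole period at the existing week 3 visit. The sentence on timing from randomisation can stay; if the window opens at randomisation, it starts where that clock starts.

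The cost is a wording change with no new visit or sample. If recording starts 7 days before the booster, look-back at week 3 grows by 7 days; starting at randomisation adds the interval before the pause. A few more SAE reports are possible. Anyone whose booster is cancelled needs one contact, because visits are tied to the booster. If recruitment has begun, sites would check records for days -7 to -1 of those already enrolled. Extending the week 3 disease-activity recall to cover the pre-booster week is optional and not needed to close the SAE gap.
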